### Outcomes assessment

The primary outcomes for this study are implementation measures [15]. The measures include the practices’ implementation Reach and Effectiveness [49]. Reach measures include the percent and characteristics of patients that: are defined as eligible to be invited to complete the MOHR assessment; are invited to complete the MOHR assessment; and complete the MOHR assessment. The primary Effectiveness measures are a comparison of early versus delayed intervention practice patient report on whether they: were asked about the health behavior and psychosocial domains; set a goal or action plan with their clinician; and arranged any follow-up contact regarding their plan. As early intervention practices will have implemented the MOHR assessment and delayed intervention practices will not yet have implemented the MOHR assessment, they will respectively serve as intervention and control conditions. The impact on health behaviors and psychosocial problems will be assessed by repeated administration of the MOHR assessment for the subset of patients providing an email address. Patient responses will be compared at baseline and four months after baseline. Multivariate regressions will assess for influences of practice implementation characteristics (*e.g.*, electronic versus paper) and patient demographics on each outcome. The overall CONSORT diagram depicting study participation and data capture are depicted in Figure 4.

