## Methods

### Overall design

The MOHR study is a paired, cluster (practice level) randomized, non-blinded, practical, implementation study that uses a delayed intervention design with 9 pairs of primary care practices (18 total). The design combines elements of pragmatic trials, implementation science, systems science, and mixed methods approaches, and engages stakeholders as partners throughout the study design, implementation, evaluation and subsequent dissemination. One practice in each pair will be randomized to early implementation, and the second to delayed implementation four months later. Implementation will consist of each practice defining a patient population and workflow and then fielding the systematic collection of the patient reported measures in daily care. The primary outcomes will be implementation measures and costs that are relevant to potential adopting and funding agencies [15-19]. Patient goal-setting and clinical follow-up in the 10 health behavior and psychosocial domains will be compared between early and delayed intervention sites prior to implementation of the MOHR assessment in delayed intervention sites, thus delayed intervention practices effectively serve as control practices. Feasibility will be assessed by monitoring implementation in both early and delayed implementation sites (see Figure 1 for project overview and timeline). The project is funded through a unique partnership of grant supplementation from the National Cancer Institute (NCI), the Agency for Healthcare Research and Quality (AHRQ), and the Office of Behavioral Social Sciences Research (OBSSR).

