### Data sources

Outcomes will be collected from three sources: practice appointment records, the Patient Experience Survey, and patient responses to the MOHR assessment. Appointment records will be used for calculating Reach (see ‘Primary outcomes’, below). Reach measures are collected when practices enter the intervention phase, months two to six for early intervention practices and months seven to nine for delayed intervention practices. Appointment records are queried by the practices (electronically or manually) for patients who meet inclusion criteria, are documented, de-identified, and transferred to a central data coordination center every two weeks. The Patient Experiences Survey will be used to compare the early versus delayed intervention practices on patient reports of patient-provider discussions, recommendations for referrals, and collaborative goal-setting across the 10 health domains. The patient responses to the MOHR assessment will be used for calculating patient health behavior and psychosocial changes over time. This will be assessed by repeated administration of the MOHR assessment for the cohort of patients who complete the assessment on the website and provide email addresses (see ‘Outcomes assessment’ , below).

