### Balancing fidelity and adaption

To maintain internal validity, certain components of the intervention were standardized. All participating practices will implement these components, and fidelity to implementation will be assessed. However, to reflect the pragmatic nature of the trial, practices were encouraged to adapt aspects of the intervention to their workflow and setting [22]. This is necessary because the MOHR study purposively includes practices that vary widely with respect to patients (mostly minority versus non-minority), location (rural versus urban), and EHR and patient portal use. Therefore, to ensure successful implementations as well as high assessment and survey response rates, each practice pair considered its patients’ needs. The elements that needed to be standardized were decided by the overall project steering committee and working groups, while decisions about local tailoring were made by the practice pairs with support and direction from the local research team.

Standard study elements include the MOHR health behavior and psychosocial assessment questions, provision of patient and provider feedback summaries based on the MOHR assessment, goal-setting materials and brief training to support clinicians with counseling, and Patient Experience Survey questions. Practice pairs are collaboratively deciding which patients to target for the MOHR assessment, while attempting to include the largest percentage of adult patients that is feasible; timing of the MOHR assessment (one to two weeks prior to a visit at the patient’s home or immediately prior to a visit at the practice); mode of the MOHR assessment (website or paper), delivery of clinician summary (integrated into EHR, faxed, printed); and mode of administering the Patient Experience Survey (postal, web-based, telephone or a combination).

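### The four-month behaviour and psychosocial result is labelled as impact, but it is an uncontrolled before-after change in website completers with email and cannot support an effect conclusion

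*Protocol article*

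**What the plan says.** In the protocol article, Outcomes assessment, the plan for this outcome is: "The impact on health behaviors and psychosocial problems will be assessed by repeated administration of the MOHR assessment for the subset of patients" who supply an email address. The contrast follows in the next sentence: "Patient responses will be compared at baseline and four months after baseline". Data sources defines the group more narrowly; the repeat is "for the cohort of patients who complete the assessment on the website and provide email addresses". Under Balancing fidelity and adaption, website or paper mode is left to each practice pair, so a pair that chooses paper contributes no one to this cohort.

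The randomised contrast is attached to a different instrument. Data sources says: "The Patient Experiences Survey will be used to compare the early versus delayed intervention practices on patient reports of patient-provider discussions", and goes on to referrals and goal-setting. Outcomes assessment applies early versus delayed to being asked about the domains, setting a goal or plan, and arranging follow-up. The regressions it adds look at practice implementation characteristics and patient demographics, and randomised condition is not named. Overall design explains the control role of the delayed arm ("thus delayed intervention practices effectively serve as control practices") and sets the lag: "One practice in each pair will be randomized to early implementation, and the second to delayed implementation four months later".

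**The concern.** The article attaches a causal label to a one-group before-after comparison. Patients complete the tool around a visit, receive feedback, and some of them answer again four months later. Any difference mixes a possible effect with four other influences: the change of season, having answered the same questions before, the timing of the first assessment relative to a visit, and the fact that those who return by email may be the more engaged patients. Nothing in the stated comparison separates these.

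At stake is what the trial may conclude on a non-primary outcome. Followed as written, it could report an effect on behaviour or mental health that would have appeared without the intervention. The limitations in the Discussion concede that long-term behavioural or biological impact cannot be examined. They do not say that the four-month change lacks a control.

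**Working it through.** The article gives no sample size, effect size or power for this analysis, so there is no figure to reproduce. The check covers design and calendar, followed by two illustrations on assumed inputs.

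**1. Is there an unexposed group with two assessments?** Delayed practices do not field the tool until they implement it (Overall design; Outcomes assessment). Their patients' first assessment is also their first exposure. No unexposed four-month change exists in either arm.

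**2. Who can be in the before-after cohort?** Inputs: delayed practices start July to September 2013, and data collection is expected to end in November 2013 (Trial status).
- July + 4 months = November 2013.
- September + 4 months = January 2014.

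If the November end also covers the emailed repeats, only the earliest delayed-practice patients can contribute a second assessment. The cohort comes mainly from early practices.

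**3. How far do the two sides overlap in calendar time?** The article supports two readings of the early baseline window.
- Figure 1 caption, early start March and delayed start July: baselines March to July, + 4 months = repeats July to November.
- Data sources, months two to six with January as month one: baselines February to June, + 4 months = repeats June to October.
- Delayed first assessments, months seven to nine: July to September.

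On either reading the overlap is July to September. It is partial, and early repeats outside those months have no concurrent counterpart.

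**4. How easily would a small drift look like an effect?** Assumptions: true effect zero, a drift of d = 0.10 SD from any non-intervention cause, within-patient correlation r = 0.5 to 0.7, N patients treated as independent, two-sided 5% test. Standard error = sqrt(2(1 - r)/N).

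| N | r | SE | d/SE | Chance of significance |
|---|---|---|---|---|
| 200 | 0.5 | 0.071 | 1.41 | 29% |
| 200 | 0.7 | 0.055 | 1.83 | 45% |
| 500 | 0.5 | 0.045 | 2.24 | 61% |
| 500 | 0.7 | 0.035 | 2.89 | 82% |

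With a 0.05 SD drift the range is 11-15% at N = 200 and 20-30% at N = 500. The nominal rate is 5%.

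**5. What could an early-versus-delayed contrast detect?** Early four-month responses are set against delayed first responses, with J = 18 practices and n usable patients per practice (assumed). Variance of the standardised difference = 4(ICC + (1 - ICC)/n)/J. The test is two-sided at 5% with 80% power. Example: n = 50 and ICC = 0.05 give 4(0.05 + 0.95/50)/18 = 0.0153, SE = 0.124, and a detectable difference of 0.37 SD on 16 degrees of freedom.

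| n per practice | ICC | Detectable, 16 df | Detectable, 8 df (paired) |
|---|---|---|---|
| 50-100 | 0.03-0.05 | 0.28-0.37 | 0.30-0.40 |
| 10-20 | 0.03-0.05 | 0.39-0.54 | 0.42-0.58 |

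The ICC values are those of the article's survey power calculation, borrowed here. All nine pairs are assumed to contribute, so paper-mode pairs would make these figures worse.

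**The case against.** The strongest defence is that this outcome is minor and partly disclaimed. The primary measures are Reach and Effectiveness, and the abstract's outcome list omits behaviour change. Data sources describes the analysis as change over time. The Discussion leaves behaviour change and health outcomes to better-funded studies. The website and email restriction is stated openly, and modelling detail for a secondary outcome can sit in a fuller document. All of this lowers the weight of the point. It does not remove it, because Outcomes assessment fixes the cohort, the contrast and the causal label together, and the label does not fit the contrast.

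Three stronger readings are tempting, and the article does not support them.

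- *The delayed practices supply a ready control, so early versus delayed should be the effect analysis.* What they supply is a single cross-sectional assessment. Early responses would be second administrations and delayed responses first ones. Delayed first assessments are tied to a visit, while early repeats come four months after baseline. Only the early side passes through follow-up loss. Paper-mode patients are still missing. Season is the one listed influence that the contrast clearly addresses, and within-patient pairing is given up.
- *Regression to the mean alone would produce 0.2-0.4 SD.* That follows from (1 - r) x 1 SD with r = 0.6 to 0.8, for patients flagged 1 SD from the mean. The planned cohort is not selected on a poor score, and these inputs have no source in the article. The figure should not be used.
- *The randomised structure of the trial is abandoned.* It is unused only in this analysis. The survey comparison keeps it.

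**Conclusion.** The point stands for a non-primary outcome. A one-group comparison at baseline and four months, in self-selected website completers with email who come mainly from early practices, cannot show an effect on health behaviours or psychosocial problems. The size of the bias cannot be derived from the article. The 29-45% and 61-82% figures depend on an assumed 0.10 SD drift, assumed correlations and assumed cohort sizes, and they show only that a modest drift is enough to mislead. That the cohort is mainly early rests on the November 2013 end date applying to the repeats. Reach and Effectiveness are unaffected. The early-versus-delayed contrast can support interpretation, but its remaining biases keep it exploratory.

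**What to change.** In Outcomes assessment, replace the word *impact* with uncontrolled within-patient change over four months among patients who completed the tool on the website and gave an email address. State that no effect conclusion will be drawn from it.

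As an exploratory supporting analysis, compare early-practice four-month responses with delayed-practice first assessments in the overlapping calendar months. Restrict both sides to website completers with email, and account for practice clustering and pair. State with the result that the contrast is cross-sectional; that repeat testing, visit timing and follow-up attrition still differ between the sides; and that early repeats outside the overlap are not used.

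The cost is wording and one added analysis, since both sets of responses are already planned. The price is a weaker claim, the early repeats lost outside the overlap, and limited precision (section 5 of the working).

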**Figure 4 F4:**
[figure not shown]
MOHR study CONSORT flow diagram.

### Power and sample size analysis

To determine power, we focused on the patient report as to whether any practice personnel worked with her/him to set specific goals for change for the 10 behavior and mental health topics. For the base power analysis, we assumed 9 matched pairs of sites, 300 patients mailed the Patient Experience Survey from each site, and a 50% response rate (2,700 total respondents). Imputation analyses will be conducted to evaluate the impact of missing data, but here we assume the loss of up to 50% of the sample for power calculation purposes. For the first power analysis, we focus on the binary event that at least one goal was established (as opposed to none). Assuming a delayed intervention response rate of 0.3, there is 90% power to detect a 17.5% improvement in the early versus delayed intervention group, and 80% power to detect a 15% improvement.

For the second power analyses, we focus on the continuous outcome of the number of goals established using a hierarchical analysis of covariance. We adjust for any baseline differences in variables related to the outcome as well as clustering effects of patients within clinic. Assuming an intraclass correlation coefficient (ICC) of 0.03, there is 90% power to detect a between conditions effect size of 0.47 with 9 sites per treatment and a 50% patient response rate, and 80% power to detect an effect size of 0.40. Assuming a larger ICC of 0.05, we have 80% power to detect an effect size of 0.51 and 90% power to detect a difference of 0.60, given the assumptions above. All power analyses were performed using the ‘Optimal Design Software’ package (version 3.0).

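### The detectable effect sizes for the number of goals (0.40/0.47 and 0.51/0.60) do not follow from the stated inputs and are about 1.4 to 1.55 times too large

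*Protocol article*

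**What the plan says.** The Overall design section describes nine pairs of practices, 18 in total: "The MOHR study is a paired, cluster (practice level) randomized, non-blinded, practical, implementation study that uses a delayed intervention design with 9 pairs". The Power and sample size analysis section starts from the same design: "we assumed 9 matched pairs of sites, 300 patients mailed the Patient Experience Survey from each site, and a 50% response rate (2,700 total respondents").

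It then reports two calculations.

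- **Binary outcome (at least one goal set).** "Assuming a delayed intervention response rate of 0.3, there is 90% power to detect a 17.5% improvement in the early versus delayed intervention group". For 80% power the figure is 15%. No ICC is given for this outcome.
- **Continuous outcome (number of goals), by hierarchical analysis of covariance.** At an ICC of 0.03, the section states that "there is 90% power to detect a between conditions effect size of 0.47 with 9 sites per treatment and a 50% patient response rate". For 80% power the corresponding figure is 0.40. At the higher ICC, 0.05, it says that "we have 80% power to detect an effect size of 0.51 and 90% power to detect a difference of 0.60".

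The section names the software package but gives no alpha, no sidedness, no assumed covariate R-squared and no allowance for pairing.

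**The concern.** The section prints both the inputs and the outputs of the continuous calculation, so it can be checked, and the outputs look too large. With 18 clusters of 150 and an ICC of 0.03 to 0.05, one expects to detect roughly a quarter to two-fifths of a standard deviation, not 0.40 to 0.60.

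Goal-setting is one of the primary Effectiveness measures, and this section is the article's only statement of what the trial can detect. If the figures are wrong, the reported sensitivity is not that of the design. A reader would think the trial able to find only moderate to large differences in the number of goals, when it could find clearly smaller ones.

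**Working it through.** **Inputs from the article.** Nine pairs, so J = 18 sites. 300 mailed × 50% response = 150 respondents per site (n). Check: 18 × 150 = 2,700, as stated. ICC (ρ) 0.03 and 0.05.

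**Assumptions.** Two-sided alpha of 5%, since none is stated, and the standard two-level cluster-randomised formula.

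**Formula.** In standard deviation units, SE = √{4[ρ + (1 − ρ)/n]/J}. The detectable effect is the SE times the noncentrality that gives the required power in a t test.

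**Standard errors with J = 18, n = 150**

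- ρ = 0.03: 0.03 + 0.97/150 = 0.03647; × 4/18 = 0.00810; SE = 0.0900.
- ρ = 0.05: 0.05 + 0.95/150 = 0.05633; × 4/18 = 0.01252; SE = 0.1119.

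**Noncentrality for 80%/90% power.** 2.985/3.455 with 16 df (J − 2); 3.201/3.712 with 8 df (nine pairs).

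**Detectable effects at 80%/90% power**

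| | ICC 0.03 | ICC 0.05 |
|---|---|---|
| Stated in the article | 0.40 / 0.47 | 0.51 / 0.60 |
| 18 sites, 16 df | 0.269 / 0.311 | 0.334 / 0.387 |
| 18 sites, 8 paired df, no gain from matching | 0.288 / 0.334 | 0.358 / 0.415 |
| 9 sites in total, 7 df | 0.416 / 0.483 | 0.517 / 0.601 |

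The stated figures are not reproduced with 18 sites. Stated divided by recomputed is 1.49, 1.51, 1.53 and 1.55 with 16 df, and 1.39, 1.41, 1.42 and 1.44 with 8 df.

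**Power at the stated effects (0.40, 0.47, 0.51, 0.60) with 18 sites.** 98.6%, 99.8%, 99.0% and 99.9% with 16 df. The paired 8 df gives 97.2% to 99.6%.

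**Could unstated choices close the gap?**

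- One-sided testing, covariate adjustment, a normal approximation and useful matching all lower the detectable effect, so they widen the gap.
- A lower response does not explain it. With 18 sites and 16 df, about 18 to 19 respondents per site would be needed for the ICC 0.03 figures and about 11 to 12 for the ICC 0.05 figures. The article assumes 150.
- A higher ICC does not explain it. Values of about 0.075 and 0.13 would be needed, against the printed 0.03 and 0.05.
- Nine clusters in total comes close but is not exact. The largest miss is 0.016, and power at the stated effects is 76.9%, 88.4%, 78.9% and 90.0%.
- A much stricter alpha also comes close. With 18 sites, 8 df and alpha of 0.007 the effects are 0.415/0.469 and 0.515/0.583, with a largest miss of 0.017.

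**Cross-check on the binary figures.** Read as percentage points (0.30 against 0.45 and 0.475), with design effect 1 + 149ρ, 9 × 150 = 1,350 respondents per arm and 16 df:

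| ICC | Power, 15 points | Power, 17.5 points |
|---|---|---|
| 0.03 | about 91% | about 97% |
| 0.05 | about 75% | about 86% |

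The stated 80% and 90% are met at ICCs of 0.0433 and 0.0439, in effect one common value inside the range used for the continuous outcome. With nine sites in total, power would be only 40–56% and 51–69% over the same ICC range. As points, then, these figures fit 18 sites.

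**The case against.** The strongest reply has three parts.

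1. **Alpha is not stated, so the mismatch depends on an assumption.** True, and every recomputed figure above carries it. But nothing in the section hints at an alpha near 0.007, and 5% is the convention a reader will apply. If a stricter level was used, its absence makes the stated power uninterpretable and it has to be printed.
2. **The error is conservative and changes nothing in conduct.** This stands. The trial is not underpowered on this account, and an eventual null result would be read from its confidence interval, not from the planning figures. It limits the consequence; it does not make the four numbers right.
3. **Pairing narrows the discrepancy.** With 8 df the ratio falls from about 1.5 to about 1.4. This also stands, and is why a range is given. It does not remove the gap.

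Two stronger readings are tempting. A reader might infer that the software was run with nine clusters in total because the per-arm count was entered as the total. That fits fairly well, but the article does not say so, the fit is inexact, and a stricter alpha with paired df fits about as well. It remains conjecture.

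A reader might also infer that the binary figures are wrong, or that the two calculations contradict each other. The document does not support this. The printed ICCs are attached to the continuous outcome. Any goal and number of goals are different outcomes that need not share an ICC, and both binary figures are consistent with 18 sites at one ICC of about 0.043. The relative reading (30% to 34.5% or 35.25%) falls short of 80% and 90% even without clustering, so points are very probably meant.

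**Conclusion.** The four detectable effects for the number of goals are wrong as written for the stated design, at a conventional alpha. On the article's own inputs they should be 0.27/0.31 (ICC 0.03) and 0.33/0.39 (ICC 0.05), or 0.29/0.33 and 0.36/0.42 if pairs are modelled with no credit for matching. This rests on a two-sided 5% alpha, which the article does not state, and on the standard two-level formula. The direction is favourable to the trial, so the fault lies in the reporting of its sensitivity and not in the adequacy of its size. How the figures arose is not established. For the binary outcome nothing is shown to be wrong; two descriptors are unclear, namely the scale of the improvement and the ICC.

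**What to change.** Rerun the continuous calculation with 18 clusters in total and 150 respondents per cluster. State alpha and sidedness, say whether pairing is in the model, and replace the four effect sizes. At two-sided 5% the replacements are the values given in the verdict. If another alpha was intended, print it and the figures that go with it.

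In the same rerun, say that the 15% and 17.5% improvements are percentage points and give the ICC behind them. Showing their power at ICC 0.03 and 0.05, as in the cross-check above, would let readers see how far they depend on it.

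The cost is one recalculation and a corrected paragraph. Enrolment, outcomes and conduct are unaffected.
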